### Adverse Events

Adverse events that meet all three of the following criteria will be reported immediately to the institution's Research Ethics Board, as is routine practice: (1) unexpected events in terms of nature, severity, or frequency; (2) events related or possibly related to participation in the research; or (3) events suggesting a potential increased risk of harm to research participants or others. All adverse events will be collected and evaluated bi-annually by the principal investigator.

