### Informed Consent

When an older adult is willing to participate in the study, a researcher approaches the subject, schedules a pre-study meeting to explain the study, and provides the study information sheet, information form for the primary care physician, and the permission to participate in the study/consent form. Participants are informed that this is a novel intervention method of a technology that aims to improve balance while riding a new stationary bicycle device, and that we hypothesize that they most likely will improve their function. In addition, they will be informed that both groups will perform bicycle training with or without perturbations thus, both are expected to improve function. To maintain the motivation of older adults to participate, they will be offered to participate in “other” exercise program after the training period. They are also informed that the training might be difficult in the beginning; thus, some muscle soreness will occur, and that participants are free to withdraw from the study at any time point, without consequence. Participants may also be withdrawn from the study due to changes in their health status that affect eligibility. A researcher will answer the participant's questions about the study, and participants may discuss the study with their family members, friends, or healthcare providers. All participants sign an informed consent statement via personal interview at enrollment. The informed consent process is documented by research personnel.

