### The Interventions

Trained physiotherapists conduct individualized training. They received training to operate the PerStBiRo system (Figure 1), and experienced it themselves to be able to determine the challenge for a participant and adjust the difficulty of the training. We use the same PerStBiRo system to train both, the PerTSBR and TSBR groups. Each group receiving 24 training sessions, twice a week for 12 weeks. Based on a recent systematic review (24) of PBBT paradigms, programs consist of low perturbation magnitudes as this is a more feasible program for each older adult, requiring longer training periods for significant improvement of reactive balance responses and reduction in fall incidence (24). Increasing the total PBBT volume increases the likelihood of its effectiveness (40). Since our PBBT program focuses on improving the trunk and arm balance recovery reactions in a sitting position, the program duration is as applied at lower magnitudes of PBBT during standing or walking, intensities that usually evoke fixed BoS strategies. Each session lasts for 20 min and includes three parts (Figure 2): stage (1) warm-up-−3 min of self-paced pedaling with the same bicycle resistance for both groups, corresponding to the training program level, without perturbations and cognitive tasks; stage (2) main exercises−15 min of perturbation training during hands-free stationary bicycling (PerTSBR). For details, see “Experimental group intervention,” with perturbations and “Control group intervention” without perturbations (TSBR) in combination with concurrent visual cognitive tasks for both groups. The graduated difficulty levels in bicycle resistance and the cognitive tasks are the same for both groups and determined according to the training program (details in Table 2); and stage (3) cool down-−2 min of self-paced pedaling without bicycle resistance, without perturbations and cognitive tasks. During stage 2 the participants are instructed to “ride the bicycle at your preferred pace and try to stabilize yourself. Try also to do your best in the cognitive tasks.” The cognitive dual-task exercises are presented using Microsoft Power Point on a TV screen 2.5 meters in front of the pedaling trainee's head. It includes tasks such as “Find the odd one out,” “Find a specific object in the picture,” and “Find the differences” between two pictures. For all tasks presented, the participant must state out loud where the object is, then have this checked by the trainer, and if the answer is correct, the next task is presented. During the training sessions trainees wear a loose safety harness that can arrest falling using the PerStBiRo system, but still allow comfortable pedaling and execution of balance recovery reactions with the upper body without the harness suspension. In both groups, each participants activities are documented in each session. See Figure 2 for a single-training session template and see detailed explanations in “Experimental intervention” and “Control intervention.”

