### Data Monitoring

A data monitoring committee is not required for this study since the PBBT is a low-risk intervention for relatively healthy older adults without cognitive impairments. Based on our previous studies, very mild adverse events related to PBBT have been reported (i.e., delayed-onset muscle soreness, fatigue, or exacerbation of joint pain) in older adults and in people with stroke (28, 70–72), but medical attention was not required. with a similar frequency and severity of adverse events for both the PBBT and control groups, who completed more “traditional” physical therapy. Therefore, the typical adverse events are not specific to the PBBT.

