## Discussion

### Strengths

This is a novel intervention method of a technology that provides self-induced and unexpected perturbations during stationary bicycle riding, which is designed to improve balance function during standing and walking among pre-frail and frail older adults. It touches on an important point in the field of fall prevention, as well as rehabilitation and motor learning principles—the ability to transfer compensatory balance reactions that are acquired in a sitting position into a target context of balance control performances in standing and walking. This study follows a strict single-blinded RCT design so that both intervention groups are trained by the same bicycle simulator system (i.e., PerStBiRo), and participants do not know which group they belong to. Both intervention groups will gain from a similar bicycling protocol consisting of endurance (pedaling intensity) and cognitive training components and, most likely, improve their function by the end of the training period. The experimental intervention consists of several exercise components with respect to motor learning, strength, endurance and, especially, balance control such as avoiding external support on the handlebars that reduces postural responses (42), increasing perturbation magnitudes to create a challenge, shifting from block to random perturbation training methods (43, 44), varied practice (43), shifting from a stable environment (simulator device is fixed) that provides external perturbations only to an unstable environment (unstable surface of the simulator device) that combines external and internal self-induced perturbations in varied training (45), giving external visual and sensorimotor cues that lead to improve intrinsic sensorimotor feedback (41). All these components provide the best possible motor learning implementation of reactive balance response in a sitting position and allow these exercises to be customized according to each subject's ability. They are challenging, but never dangerous. Our training is designed for a 12-week intervention period, with each training session lasting about 20 min, which is a similar time to conventional physical therapy training, so that in future clinical applications, it can be fit in a standard physical therapy session.

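### Half-yearly collection and evaluation of adverse events does not fit a 12-week training course: mild events may be incompletely captured, and a rise in their frequency seen late

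*Protocol article*

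**What the plan says.** The Adverse Events section gives two routes.

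- **Immediate:** "Adverse events that meet all three of the following criteria will be reported immediately to the institution's Research Ethics Board, as is routine practice". The criteria concern unexpectedness (in nature, severity or frequency), relation to the research, and a possible increase in risk.
- **Everything else:** "All adverse events will be collected and evaluated bi-annually by the principal investigator".

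Exposure is set in The Interventions: "Each group receiving 24 training sessions, twice a week for 12 weeks". The same section says "Trained physiotherapists conduct individualized training" and "In both groups, each participants activities are documented in each session".

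Table 1, the schedule of assessments, has a row for monitoring during training. It covers balance recovery (experimental arm only), the cognitive dual task and bicycle resistance. Adverse events appear neither there nor at T1 or T2.

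On oversight, Data Monitoring says "A data monitoring committee is not required for this study since the PBBT is a low-risk intervention". It names the mild events seen in earlier studies: delayed muscle soreness, fatigue and worsening joint pain.

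**The concern.** The sentence on adverse events puts collection as well as evaluation on a half-yearly cycle, in a trial where a participant's whole course takes less than half of that cycle. Followed literally, many participants would start and finish training between two collection points. Their milder complaints would then depend on recall weeks or months later.

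Two things are at stake. The first is completeness: the trial's own safety data are its means of testing the low-risk premise for a new device, and the statement in the Strengths section that the exercises are never dangerous ("They are challenging, but never dangerous"). The second is timeliness: with no monitoring committee and no planned interim analysis of outcomes, the half-yearly review is the only aggregate look at safety that the article describes. A growing frequency of complaints could go unseen while the participants concerned are still training.

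**Working it through.** The article gives no figure for adverse-event review, so there is none to reproduce.

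**Inputs from the article**
- Training: 12 weeks = 84 days (The Interventions).
- Review interval: *bi-annually*, read as twice a year, so about 182 days or 26.09 weeks (Adverse Events).
- Planned sample: 68 (Participants).
- Study period: 1 March 2019 to 31 December 2021, which is 148 weeks (Trial Status).

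**Assumptions not in the article**
- Participants enter uniformly over time.
- Reviews fall on fixed calendar dates.

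**Share of participants with no review during training**
- Formula: 1 − (training length ÷ review interval).
- (182 − 84)/182 = 98/182 = 54%.
- 0.54 × 68 ≈ 37 participants.

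**The same share over the actual study period**
- The last participant must start by week 148 − 12 = 136.
- In each 26.09-week interval, entrants in the first 26.09 − 12 = 14.09 weeks finish before the next review.
- Five full intervals cover 5 × 26.09 = 130.45 weeks. The remaining 136 − 130.45 = 5.55 weeks of entry also have no review during training.
- (5 × 14.09 + 5.55)/136 = 76.0/136 = 56%. A simulation gave the same value.

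**Number of reviews and delay**
- 148/26.09 = 5.7, so five reviews fall within the study period.
- For an event at a random time, the mean wait to the next review is 26.09/2 ≈ 13 weeks, and the longest about 26 weeks.

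**Participants who finish before the first review of the trial**
- 14.09/136 = 10%.

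**Sensitivity to the review interval**
- If *bi-annually* meant every two years (104.36 weeks), the same formula gives 1 − 12/104.36 = 88.5%.
- At 13 weeks the share is 1 − 12/13 = 7.7%. At 12 weeks or less it is zero.

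**Does the immediate route fill the gap?**
- The lead-in requires all three criteria, and the first is unexpectedness. Soreness, fatigue and joint pain are anticipated in Data Monitoring, so a single such event would normally not qualify.
- An unexpected frequency would satisfy the first criterion, but a frequency becomes visible only when events are collected and counted. To that extent the fast route depends on the slow one.

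**The case against.** **Central collation.** The sentence may mean only that the principal investigator gathers and reviews accumulated reports twice a year. Physiotherapists run every session, activities are documented each time in both arms, and immediate reporting presupposes that somebody notices events as they occur. This is a fair reading, and it makes it unlikely that serious events would go unnoticed for months. However, none of those passages names adverse events, and the sentence attaches the interval to collection too. If only evaluation was meant, the sentence still needs correcting.

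**Condensed article.** Form layout and question wording belong in the full protocol, and the missing row in Table 1 would be no finding alone. But the interval is not left out: it is stated, and does not fit the exposure. Table 1 matters only because it offers nothing to offset the rule.

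**Scope of the immediate route.** Its lead-in requires all three criteria, yet they are joined by *or*. If any one sufficed, soreness related to training could qualify and the gap would narrow. That ambiguity is a separate point.

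**Stronger readings that the document does not support**
- *Harms cannot be compared between arms.* Recorded events can be tabulated by arm at study end, and the same interval applies to both arms. The interval alone creates no difference between them.
- *Most participants finish before any review.* The 54% is a bare majority resting on assumed entry and review dates. Only about 10% finish before the trial's first review.
- *Adverse events are looked at only twice a year.* This ignores the immediate route and the supervised sessions.
- *A harmed participant would leave unrecorded.* Informed Consent says "Participants may also be withdrawn from the study due to changes in their health status that affect eligibility", but nothing says that the event behind a withdrawal goes unrecorded. The withdrawal rule needs no change on this ground.

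**Conclusion.** The point holds as a badly set rule on recording and review. Read literally, the half-yearly cycle leaves slightly more than half of participants (54%, or 56% over the actual study period) without a collection or review point during their 12 weeks of training. These figures rest on uniform entry, fixed calendar reviews and *bi-annually* meaning twice a year. The consequence is possible under-capture of mild, expected events and late notice of a rise in their frequency. How many events would be missed cannot be calculated from the article. Serious, unexpected and related events have their own route, and an end-of-study comparison by arm remains possible. The correction is worth making because the rule is explicit and the remedy cheap.

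**What to change.** - **Separate the two activities in Adverse Events.** State that recording is continuous and evaluation periodic.
- **Recording.** Ask one fixed adverse-event question at every training session and at T1, T2 and any withdrawal, identically in both arms. Enter the answer on the session documentation that already exists, and add a row to Table 1. A common question matters because balance recovery during training is monitored in the experimental arm only, so events noticed in passing could differ between arms.
- **Evaluation.** Have the principal investigator review the accumulated events at a clearly stated interval shorter than the 12-week course. Replace *bi-annually* with a number of weeks.
- **Reporting.** Report events by arm.

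The cost is one line on the session form, one table row and revised wording, plus more frequent review by the principal investigator. No extra participant visits are needed. There is a small downside: more minor events will be recorded, and the trainers who ask the question know the arm, so reports of mild symptoms should be read with that in mind.

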### Data Monitoring

A data monitoring committee is not required for this study since the PBBT is a low-risk intervention for relatively healthy older adults without cognitive impairments. Based on our previous studies, very mild adverse events related to PBBT have been reported (i.e., delayed-onset muscle soreness, fatigue, or exacerbation of joint pain) in older adults and in people with stroke (28, 70–72), but medical attention was not required. with a similar frequency and severity of adverse events for both the PBBT and control groups, who completed more “traditional” physical therapy. Therefore, the typical adverse events are not specific to the PBBT.

### Trial Status

The study is currently recruiting participants. Enrollment began on March 1, 2019. We will complete the recruitment, training, and T1 and T2 data collection by December 31, 2021. We will complete the data analysis by December 31, 2022.

## Discussion

### Strengths

This is a novel intervention method of a technology that provides self-induced and unexpected perturbations during stationary bicycle riding, which is designed to improve balance function during standing and walking among pre-frail and frail older adults. It touches on an important point in the field of fall prevention, as well as rehabilitation and motor learning principles—the ability to transfer compensatory balance reactions that are acquired in a sitting position into a target context of balance control performances in standing and walking. This study follows a strict single-blinded RCT design so that both intervention groups are trained by the same bicycle simulator system (i.e., PerStBiRo), and participants do not know which group they belong to. Both intervention groups will gain from a similar bicycling protocol consisting of endurance (pedaling intensity) and cognitive training components and, most likely, improve their function by the end of the training period. The experimental intervention consists of several exercise components with respect to motor learning, strength, endurance and, especially, balance control such as avoiding external support on the handlebars that reduces postural responses (42), increasing perturbation magnitudes to create a challenge, shifting from block to random perturbation training methods (43, 44), varied practice (43), shifting from a stable environment (simulator device is fixed) that provides external perturbations only to an unstable environment (unstable surface of the simulator device) that combines external and internal self-induced perturbations in varied training (45), giving external visual and sensorimotor cues that lead to improve intrinsic sensorimotor feedback (41). All these components provide the best possible motor learning implementation of reactive balance response in a sitting position and allow these exercises to be customized according to each subject's ability. They are challenging, but never dangerous. Our training is designed for a 12-week intervention period, with each training session lasting about 20 min, which is a similar time to conventional physical therapy training, so that in future clinical applications, it can be fit in a standard physical therapy session.

### Weaknesses

In this study, we aim to improve balance control and balance reactive components by tilting perturbations. However, these tilting perturbations during bicycle riding may not be similar enough to balance loss situations that cause falls among older adults; thus, they may not be specific. Because of the lack of specificity in this model, we may find no effects of the intervention. Perturbations in the experimental group are limited to the ML direction only, while hip balance strategy, which is one target of this training method, are triggered mainly by anterior–posterior movements. Trainers are trained to follow the pedaling intensity according to the training program to control this endurance component in the two intervention groups, but although the bicycle resistance is set equally, it might be difficult to monitor the speed of pedaling for each participant. This program is less challenging than the PBBT in walking and standing, but it is still possible for older adults to have difficulties in hands-free riding or to progress very slowly in the training program, which may not be enough to lead to improvement. Lastly, since the PBBT is a challenging training approach, there is a risk that older adults will stop participating in the program (drop out). In regard to our RCT study, there are disadvantages (limitations) to the convenience sampling that may weaken this study. The convenience sampling can lead to the under-representation or over-representation of particular groups within the sample. For example, old volunteers that commits to train 3 months are different from the general population of older adults. This undermines our ability to generalize our results to the general population of older adults. However, in our RCT the participant is randomly allocated to two groups thus a significant improvement in balance control system in one of the groups may truly represent a change in the balance function.

## Ethics Statement

The studies involving human participants were reviewed and approved by Soroka University Medical Center. The patients/participants provided their written informed consent to participate in this study. Written informed consent was obtained from the individual(s) for the publication of any potentially identifiable images or data included in this article.

## Abbreviations

PBBT: Perturbation-based-balance training
BoS: Base of support
RCT: Randomized controlled trail
ML: Medio-lateral
PerTSBR: Perturbation training during stationary bicycling riding
TSBR: Training of stationary bicycle riding without perturbations
PerStBiRo: Perturbation stationary bicycle robotics
TV: Television
CoM: Center of mass
ICC: Intra-class correlation
AP: Anterior—Posterior
LLSS: Loaded leg side step
ULSS: Unloaded leg side step
COS: Crossover step
3D: Three-dimensional
EO: Eyes open
EC: Eyed closed
CoP: Center of pressure
SDA: Stabilogram-diffusion analysis
BBS: Berg Balance Scale
6MWT: Six-Minute Walk Test
LLFDI: Late Life Function and Disability Instrument
FES-I: Falls Efficacy Scale-International
MMSE: Mini Mental State Examination
ANOVA: Analysis of variance
SE: Effect size
Ct: Critical time (SDA parameter)
Cd: Critical displacement (SDA parameter)
Ds: Short-term effective diffusion coefficients (SDA parameter)
Dl: Long-term effective diffusion coefficients (SDA parameter).
